#### Randomisation

The stepped wedge design is a one-way crossover design in which different clusters cross over (switch treatments) at different time points (Mdege et al., 2011). In addition, the clusters cross over in one direction only—typically, from control to intervention. The first time point usually corresponds to a baseline measurement where none of the clusters receive the intervention of interest. At subsequent time points, clusters initiate the intervention of interest and the response to the intervention is measured. More than one cluster may start the intervention at a time point, but the time at which a cluster begins the intervention is randomized (Brown and Lilford, 2006, Hussey and Hughes, 2007).

Enrollment: participating physiotherapists will be recruited by the lead researcher by invitation on the basis of inclusion criteria. They will be approached by the lead researcher, and issued with participant information sheet version 2.0 (see appendix C). The lead researcher will also obtain written consent with participant consent form version 2.0 (see appendix C). During data collection periods, patients will be recruited by their physiotherapist, and issued with patient information sheet version 1.0 (see appendix B). The physiotherapist will also obtain written consent with patient consent form version 1.0 (see appendix B).

Sequence generation: once consented by the lead researcher, participating therapists will be directed to the clinical mentors. The clinical mentors will then randomly allocate the clusters of physiotherapists (clustering by site) to the sequence of intervention (to receive the intervention in time period 2, 3 or 4), by computer programme (Randomization.com, 2008).

Allocation concealment: The sequence generation will be performed by the allocated mentor, in order to ensure that this sequence allocation will be adequately concealed from the lead researcher, who will remain blinded to the sequence until after the data collection and analysis period is completed. These measures for blinding, sequence generation and allocation concealment are implemented to reduce the risk of bias, as highlighted by the Cochrane risk of bias tool (Armijo-Olivo et al., 2010, Lundh and Gotzsche, 2008).

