### **Blinding (Masking)**

As with all other evaluations, masking patients, caregivers and observers, as well as those undertaking the statistical analysis is important in minimising information bias (Schulz et al., 2002, Schulz and Grimes, 2002). Due to the fact that in stepped wedge trials the timing of intervention rollout is the unit of randomization, the participating physiotherapists and intervention implementers (clinical mentors) are aware of which cluster is receiving the intervention (Brown et al., 2008, Mdege et al., 2011). However, it is possible to blind the outcome assessors, in this case the lead researcher (who will be unaware of the sequence allocation when analysing outcome data) and the independent observer of physiotherapist performance. This blinding of outcome assessors and use of sequence generation and allocation concealment is essential to enhance internal validity (Brown et al., 2008). Patients submitting their outcomes will also be unaware of whether or not their allocated physiotherapist has received his/her intervention.

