#### Semi-structured interviews

Murphy et al (Murphy et al., 1998) identify the use of interviews in scenarios where researchers seek to discover what people think about the world they live in, how they evaluate their experiences within it and why they behave as they do, interpreting the choice to use interviews to collect data as, “If you want to understand what people do, believe and think, ask them” (p112 Murphy et al., 1998). Qualitative interviews allow relatively rapid data collection based on what interviewees say about their beliefs and attitudes, action and behaviour (Pope and Mays, 2006). Miles and Huberman (1984), Noaks and Wincup (2004) and Silverman (2010) strongly suggest that researchers do not present their main research question directly to the respondents themselves on the basis that this can affect their responses, and can lead to simply reporting back what respondents have told you instead of undertaking and reporting careful data analysis. Bearing this in mind, the general aim of the interviews in this study is to encourage the participants to speak personally and at length about their professional development as physiotherapists, while at the same time covering the issues which are of interest in answering the research questions – namely, to explore the participants’ and mentors’ experiences about the interventions in the study - mentoring and training, and their evaluation of both. As a result, there will need to be a balance maintained between what is interesting to the researcher and what is interesting to the participant (Silverman, 2006). To meet this aim, face-to-face interviews with participants and mentors will be conducted at the end of the intervention period. The closeness of the lead researcher to the clinic sites will allow for this rather than needing to interview participants by telephone. The subsequent questions that arise are what type of interview to employ and whether to perform interviews individually or to utilize focus groups to gain these reports from participants?

Several authors have sought to discuss the distinction and differences between structured and unstructured interviews (Burgess, 1982b; Habermann-Little, 1991; Fontana and Frey, 1994). However, some authors (Murphy et al., 1998, Britten, 2006) challenge the term ‘unstructured’ as misleading due to the impossibility of conceiving an interview which is totally without structure, and acknowledging that without structure

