Another reason to include participant observations in this study is the complementarity with interviews. While interviews will provide information, there can be no assurance that what participants say they do is what they actually do and observation goes some way to addressing this problem (Pope and Mays, 2006, Silverman, 2006). It is now commonplace in health research to use observations to corroborate and nuance interview findings (Keen, 2006).

Qualitative observations of the mentoring process will allow the lead researcher to position himself in the process of the mentoring and take field notes on the behaviour and activities of participants and their mentors during the delivery of clinical reasoning facilitation. The lead researcher will be able to record (in the field notes and with audio recording) the dynamic between mentor and participant, as well as to directly witness the intervention in progress. The data obtained from the observations will be used in conjunction with that from interviews to develop themes which in turn will be triangulated with that of the quantitative methods (see mixed methods data analysis procedures section).

The lead researcher's presence may be perceived as intrusive by the participant and / or the mentor; one half day observation per mentor/participant should be sufficient to provide the qualitative data required, without disrupting the majority of the delivery of the clinical reasoning facilitation.

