#### **Costs of usual training and clinical reasoning programmes**

Overall costs of providing the training programmes will be computed and include the costs of implementing and delivering the programmes and any costs incurred by participants (e.g. Transport to another site to receive training). The overall cost per participant will be computed, for the overall study and for each site. However, a clear demarcation will be made between set up costs, implementation costs and those that would occur if the programmes were to become part of subsequent mainstream provision.

The costs of implementing and delivering the programmes will include staff time, venue and equipment costs, provision of support facilities, materials utilised etc.

As mentors and trainers are supplied from within the physiotherapy service, the staffing costs associated will be readily available. Therefore the actual salary costs of mentors will be obtained and then multiplied by the hours of non-patient contact time as part of the mentoring to derive the average staffing costs for facilitators. The non-patient contact time of mentees will also be calculated in the same way. The Monthly Training Requirements Form (Appendix F) will be entered into an Excel database, which will be forwarded to the lead researcher for analysis with assistance from the research supervisor. This would generate the information necessary for computing the cost associated with providing each mentoring programme.

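### The protocol says the lead researcher stays blind to the rollout order through analysis, but his own observation and interview duties reveal that order by step 3

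*Protocol*

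**What the plan says.** The Randomisation section, under allocation concealment, describes the lead researcher as someone "who will remain blinded to the sequence until after the data collection and analysis period is completed". Blinding (Masking) lists among the blinded outcome assessors "the lead researcher (who will be unaware of the sequence allocation when analysing outcome data", and treats this blinding as essential to internal validity. To keep the order from him, the same Randomisation section gives the task to others: "The clinical mentors will then randomly allocate the clusters of physiotherapists (clustering by site) to the sequence of intervention".

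The qualitative component gives the same person these duties:

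- Under Observations: "Qualitative observations of the mentoring process will allow the lead researcher to position himself in the process of the mentoring and take field notes". The extent is given as "one half day observation per mentor/participant should be sufficient to provide the qualitative data required". Table 2, the form he fills in, records time and date, location, participant and mentor.
- Under Semi-structured interviews: "face-to-face interviews with participants and mentors will be conducted at the end of the intervention period". The section relies on the lead researcher being close to the sites. It rejects focus groups partly because start and finish times are staggered by the design and some participants would wait too long.
- Under Mixed Methods Definition, the qualitative and quantitative data are collected at the same time, so the qualitative work is not held back until after the analysis. Mixed methods data analysis procedures describes a single-researcher project.

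**The concern.** Mentoring in the 150-hour form happens in a cluster only once that cluster has crossed over. Anyone who watches it knows which site pair has crossed over and when, and that is the randomised sequence. The protocol therefore credits the trial with a safeguard that its own procedures remove.

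The safeguard matters because the protocol leaves the analyst some freedom. Risk Adjustment builds the covariate model by backward deletion and does not say when that step is done. Statistical methods, repeated under Challenges in using this design, allows a within-cluster analysis if no temporal effects are found. In a stepped wedge, time and intervention move together, so that choice can shift the estimate. A reader who accepts the blinding statement would believe these choices were made without knowledge of who was treated when.

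**Working it through.** The plan gives no figure on this point to reproduce. The power calculation (0.805 with 432 observations) does not depend on blinding and is unaffected.

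**Who knows what, and when.** The Intervention section puts mentoring at the start of each step and data collection at the end. Challenges in using this design sets each step at 12 months. So an observation of mentoring in a step comes before that step's outcomes are collected.

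**Orders left.** Randomisation assigns 3 clusters to time periods 2, 3 or 4, which gives 3! = 6 orders.

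**Cluster-steps of unknown status.** There are 3 clusters × 4 steps = 12 cluster-steps. All 3 in step 1 are control and all 3 in step 4 are intervention, whatever the order. Blinding to the sequence can therefore hide only 12 − 6 = 6 of them, those in steps 2 and 3. Once the step-2 cluster is known, step 2 is fully known. In step 3 the first cluster is known to be on intervention, which leaves 2 unknown.

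| Mentoring seen by the lead researcher in | Orders left | Cluster-steps of unknown status |
|---|---|---|
| no step | 3! = 6 | 6 |
| step 2 | 2! = 2 | 2 |
| steps 2 and 3 | 1! = 1 | 0 |

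The full order is known during step 3, before the step-3 and step-4 outcomes are collected and well before the final analysis. This does not need every therapist to be observed. Seeing any two clusters mentored fixes the position of the third. If only one cluster were ever observed, two orders would remain. The interviews, held along the staggered rollout, give the same information again.

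**What the analyst can still choose.** The within-cluster option shows why this matters. Suppose outcomes drift by δ PSFS points per step for reasons unrelated to mentoring (linear drift is an assumption; the protocol gives no value). The mean intervention step minus the mean control step is:

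- crossing in period 2: (2+3+4)/3 − 1 = 2
- crossing in period 3: (3+4)/2 − (1+2)/2 = 2
- crossing in period 4: 4 − (1+2+3)/3 = 2

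A within-cluster difference of means without time effects therefore carries a bias of 2δ. A drift of half a point per step would by itself produce the 1-point effect that the trial is sized to detect. This weakness belongs to the option and exists for a blind analyst too. It shows that the decision is not trivial and should not rest on a blinding that is absent.

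**The case against.** The best case for the protocol has several parts, and much of it stands.

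- **Covariate choice.** A reader might infer that an unblinded analyst could pick covariates to suit the result. Risk Adjustment takes the screening data from step 1, when every cluster is control, so knowing the order says nothing about treatment in those data. What remains is only that the backward deletion is not dated.
- **Time effects.** Challenges in using this design commits to both within- and between-cluster analysis and to time effects in the model. The discretion is therefore narrower than Statistical methods alone suggests. The conditional option still stands in both sections.
- **Mentors generating the order.** A reader might infer that this serves no purpose once the lead researcher is unblinded. It does serve one. He recruits and consents the therapists, and having someone else generate the order keeps it from him until consent is complete. A reader might also suspect that an unlogged allocation could be repeated until a preferred order came up. Nothing in the protocol suggests this, and no motive for preferring one order is apparent.
- **Training-hours data.** The mentoring time forms go into a database "which will be forwarded to the lead researcher for analysis with assistance from the research supervisor". This looks like a third route, but no forwarding date is given and it could follow the analysis. The point does not rest on it.
- **Recorded scores.** A reader might infer that knowing the order early biases the outcomes. The documents do not support that. The PSFS is completed by the patient with the treating physiotherapist, and therapist performance is scored by an independent assessor.

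None of this reconciles the blinding statements with the observation and interview duties.

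**Conclusion.** The claim that the lead researcher is blind to the sequence through data collection and analysis is wrong as written. He knows the whole order by step 3, and the claimed blinded analysis does not exist. This assumes that he carries out the observations as the protocol describes, in at least two of the three clusters and at the time of mentoring.

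The size of the problem is limited. It concerns two analytic choices, the undated backward deletion and the within-cluster option. It does not concern the recorded scores or the concealment of the order at therapist enrolment. No bias in the estimate can be quantified from the document. The finding is that a stated protection is absent, and it should be corrected and replaced by fixing the analysis in advance.

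**What to change.** 1. In Randomisation and Blinding (Masking), state that the lead researcher is blind to the order only until therapists have consented and is unblinded from step 2. Withdraw the claim of blinded outcome analysis.
2. Fix the primary model, with time effects always included and no switch to a within-cluster-only analysis. Fix the covariate set from step-1 data. Lock both, with the analysis code, before any step-2 outcome data are opened.
3. Optionally, have someone who neither delivers mentoring nor analyses outcomes generate the order once, after consent, and log it. Whoever generates the order should not be described as a masked analyst. Masking site labels would not restore blinding either, because the model in Power calculation: summary needs the indicator of when each unit crosses over.

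The qualitative component can stay as it is. The cost is small: some analysis work is brought forward and the blinding statement becomes less favourable.

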### **Blinding (Masking)**

As with all other evaluations, masking patients, caregivers and observers, as well as those undertaking the statistical analysis is important in minimising information bias (Schulz et al., 2002, Schulz and Grimes, 2002). Due to the fact that in stepped wedge trials the timing of intervention rollout is the unit of randomization, the participating physiotherapists and intervention implementers (clinical mentors) are aware of which cluster is receiving the intervention (Brown et al., 2008, Mdege et al., 2011). However, it is possible to blind the outcome assessors, in this case the lead researcher (who will be unaware of the sequence allocation when analysing outcome data) and the independent observer of physiotherapist performance. This blinding of outcome assessors and use of sequence generation and allocation concealment is essential to enhance internal validity (Brown et al., 2008). Patients submitting their outcomes will also be unaware of whether or not their allocated physiotherapist has received his/her intervention.

### **Statistical methods**

The analysis of stepped wedge trials has been clearly outlined in a published paper (Hussey and Hughes, 2007) and recommends processes for analysis of cluster-level means and individual level analysis in scenarios where cluster sizes are equal or unequal, and where variance is known or unknown. Processes for between cluster and within cluster analyses are outlined in order to avoid confounding the treatment effect with changes over time; these processes will form the basis for the statistical analysis for the study. If no temporal effects are found influencing the outcome, then a within-cluster analysis can be used to estimate the treatment effect. Statistical analysis will involve a classical ANOVA (so observations belong to one of two groups, each assumed to be independent of the others), supplemented by a random intercept which will reflect systematic differences across different clusters. Similar statistical methods have been used in other published stepped wedge trials (Schnelle et al., 1992, Bailey and Archer, 2004, Mdege et al., 2011).

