### Eligibility criteria for participant clusters

As expertise is generally accepted to be context dependent (Alderson, 2010, Benner et al., 1996, Edwards and Jones, 2007, Eraut, 2006b, Jensen et al., 2007b, Resnik, 2007), all qualified physiotherapy staff from the Cardiff and Vale University Health Board whose majority of time (i.e. greater than 50%) is practised inside the musculoskeletal outpatient context will be eligible to participate in this study. There are two main exclusion criteria, namely members of staff who have already undertaken postgraduate placements as part of Master's education and so would have received similar clinical reasoning facilitation, and rotational staff due to the fact that they will not be present in the department for long enough for both interventions and long term follow up. Currently, the maximum potential number of participating therapists would be 18. It is envisaged that 12 physiotherapists would realistically be recruited and organized into 3 clusters of physiotherapy staff (clustering by site).

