## Sample size

The primary outcome measure, the PSFS, shows that for any individual patient, the minimal detectable change (90%CI) for an aggregate of 3 or more activities is 2 points; the minimum detectable change (90%CI) for a single activity is 3 points. In this study, we are looking for a mean difference of 1 point greater improvement in PSFS scores of patients whose physiotherapists who have received the intervention compared with the PSFS scores of patients whose physiotherapists have not yet received the training, as well as a greater proportion of patients achieving the level of minimal detectable difference. The following data values were used for the power calculation: mean changes on the PSFS from usual training to the new training of 1 point, and a Standard Deviation within each group of 2. The standard deviation was on the basis of PSFS data collected from an audit of 191 patients who had received treatment at the University Health

Board physiotherapy department, which is a slightly more conservative estimate than standard deviation values of PSFS outcomes from published studies (Hefford et al., 2009, Young et al., 2010, Costa et al., 2009).

A paper published on the design and analysis of stepped wedge designs (Hussey and Hughes, 2007) investigated the statistical characteristics of the stepped wedge design for CRCTs, and through the use of theoretical calculations and simulation the authors outline a procedure for computing power in stepped wedge trials. Using this procedure, a power calculation was carried out by [name], Senior Lecturer in Statistics, Swansea University in discussion with the rest of the research team. The power calculation is summarised below:

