### **Power calculation: summary**

Following the notation of Hussey & Hughes (Hussey and Hughes, 2007), and defining

- I to be the number of physios (the maximum available would be 18; assuming recruitment of two-thirds of the maximum to be a realistic prospect, so we are primarily interested in  $I = 12$ )
- T to be the number of time points (4 time points are required to allow baseline measures and for 3 clusters to cross over from control to intervention, so we are primarily interested in  $T = 4$ )
- N to be the number of observations per physiotherapist per time point.

The model is

$$Y_{ijk} = \mu + \alpha_i + \beta_j + \theta X_{ij} + \varepsilon_{ijk}$$

where  $Y_{ijk}$  is the  $k^{th}$  observation at time  $j$  for physiotherapist  $i$ , and we assume that there is a random physiotherapist effect, so

$$\alpha_i \sim N(0, \tau^2)$$

and some random variation across observations, so

$$\varepsilon_{ijk} \sim N(0, \sigma_\varepsilon^2)$$

with independence everywhere. The  $X_{ij}$  are indicator variates, with value 0 before the intervention, and the value 1 thereafter. The range of indices are  $i = 1, \dots, I; j = 1, \dots, T$  and  $k = 1, \dots, N$ . We take  $\beta_T = 0$  in order to avoid identifiability problems, and wish to consider  $\vartheta$ , the difference in means in the control and intervention group. The variance of  $\hat{\vartheta}$  is given in equation (8) in Hussey & Hughes (Hussey and Hughes, 2007), and its calculation requires the specification of  $\sigma_\varepsilon^2$  and  $\tau^2$ , with  $N$  appearing through

$$\sigma^2 = \frac{\sigma_\varepsilon^2}{N}$$

Omitting some algebra, statistical power, based on the usual 95% confidence level, is defined by

$$1 + \Phi(-1.96 - \Delta) - \Phi(1.96 - \Delta)$$

where

$$\Delta = \frac{\theta_A}{\text{Var } \hat{\theta}}$$

and  $\Phi(\bullet)$  is the usual cumulative distribution function for the standard Normal distribution, and is implemented in EXCEL as =NORMSDISTO.

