#### Base case details

- Here, we take  $\theta = 1$  (that is, assume that the average effect of the intervention is 1), and (based on calculations on previous data) set  $\sigma_\varepsilon = 2$ . The remaining calculations are laid out in the attached spreadsheet, where, for illustration, if we take  $N = 9, \tau = 1$  then

$$Var(\hat{\theta}) = 0.12576 \dots,$$

and

$$\Delta = 2.819574$$

so that the power is

$$1 + \Phi(-1.96 - 2.8196) - \Phi(-1.96 - 2.8196) \simeq 1 - \Phi(0.8596) \simeq 0.805$$

- This implies that, in order to achieve a power of 0.8, we need a total of  $4 \times 12 \times 9 = 432$  observations.

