### **Challenges in using this design and how they will be addressed**

The main challenge associated with the design, conduct, analysis, and interpretation of CRCTs compared with individually randomized trials, is that two different units of measurement—the cluster and the patient—are used (Campbell, 2004). To address this, each will need to be reported carefully.

There are also several challenges raised by the stepped-wedge design. The first group of challenges are statistical. The unidirectional aspect of the crossover in the stepped-wedge design complicates the analysis because the treatment effect can no longer be estimated exclusively from within-cluster comparisons; within-cluster analysis has the potential for bias where the estimated treatment effect may be biased due to failure to model time effects (Hussey and Hughes, 2007). This will be addressed by performing both within-cluster and between-cluster analysis in order to estimate the treatment effect. This approach avoids confounding the treatment effect with changes over time; however, if there are no temporal effects on the outcome then within-cluster analyses can be used to estimate the treatment effect. In addition, time effects will be included in the model for analysis as suggested in the literature (Hughes, 2007, Hussey and Hughes, 2007, Brown et al., 2008).

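### The protocol contradicts itself on calendar time: the power model includes period effects, but the analysis text allows time to be dropped when no temporal effect is found

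*Protocol*

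**What the plan says.** Four statements in the protocol bear on whether calendar time is in the analysis.

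- **Power calculation: summary.** The model for each observation has a random physiotherapist effect, a fixed effect for each time point and the intervention effect. Time is in the model.
- **Statistical methods.** Between- and within-cluster processes are to be used so that treatment is not confounded with time. Then: "If no temporal effects are found influencing the outcome, then a within-cluster analysis can be used to estimate the treatment effect".
- **Statistical methods, next sentence.** "Statistical analysis will involve a classical ANOVA (so observations belong to one of two groups, each assumed to be independent of the others"), with a random intercept for cluster differences. No period term is named.
- **Challenges in using this design.** This section warns that a within-cluster estimate may be biased if time is not modelled and promises both types of analysis. It then repeats the permission ("if there are no temporal effects on the outcome then within-cluster analyses can be used to estimate the treatment effect") and follows it with "In addition, time effects will be included in the model for analysis as suggested in the literature".

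No test, threshold or criterion for deciding that there are no temporal effects is given.

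**The concern.** In a one-way crossover, the later a patient is seen, the more likely the physiotherapist has been mentored. Steps last 12 months, so the four steps span four years. A slow change in referral mix, staffing or general practice over that time looks like an intervention effect unless period is in the model.

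The protocol's answer to history threats is that all sites share the same external events. A shared trend is exactly what contaminates a no-period estimate, so that answer does not help here.

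Failing to find a trend is also weak evidence that there is none. If the analyst tests for time and drops it when the test is negative, the primary comparison can be both biased and reported with too small a standard error. Two analysts who follow different sentences of this protocol could report different primary estimates.

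**Working it through.** **Inputs from the protocol.** Two-sided 5% level ("statistical power, based on the usual 95% confidence level, is defined by"; z = 1.96). Effect 1 point ("assume that the average effect of the intervention is 1"). SD 2 ("a Standard Deviation within each group of 2"). N = 9 per physiotherapist per period and tau = 1 (Base case details). T = 4. I = 12 ("It is envisaged that 12 physiotherapists would realistically be recruited and organized into 3 clusters of physiotherapy staff"), taken as 4 per sequence.

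**Assumptions, because the protocol gives no figure.** A linear drift d in PSFS points per 12-month step, ranging from 0 to 0.75. A 5% test of time, either 3-df (period as a factor) or 1-df (linear trend). Period is kept if the test is significant and dropped otherwise. True intervention effect 0.

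**Step 1: reproduce the stated power.** With sigma² = 4/9 = 0.4444, U = 24, W = 224, V = 56:

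- Var = I·sigma²·(sigma² + T·tau²) / [(I·U − W)·sigma² + (U² + I·T·U − T·W − I·V)·tau²]
- = 5.3333 × 4.4444 / (28.444 + 160) = 0.125786, so SE = 0.3547
- Delta = 1 / 0.3547 = 2.8196; power = 0.805; observations = 4 × 12 × 9 = 432

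This matches Base case details and Appendix E. The variance is the one with period effects included.

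**Step 2: bias if period is left out.** Regress time on the intervention indicator within each sequence, both centred on their sequence means:

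| Sequence | Indicator over steps 1–4 | Cross-product with time | Sum of squares |
|---|---|---|---|
| 1 | 0,1,1,1 | 1.5 | 0.75 |
| 2 | 0,0,1,1 | 2.0 | 1.00 |
| 3 | 0,0,0,1 | 1.5 | 0.75 |
| Total | | 5.0 | 2.50 |

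Bias = (5.0 / 2.5) × d = 2.0 × d. A drift of 0.25 points per year gives 0.5 points, half the 1-point target. With a random intercept at tau = 1 the multiplier is about 1.96.

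**Step 3: apparent precision without period.** With 4 physiotherapists per sequence the sum of squares is 4 × 2.5 = 10, so SE = √(0.4444 / 10) = 0.211. The random-intercept version gives 0.209. Both compare with 0.355 when period is included.

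**Step 4: type I error of the test-then-drop rule, by simulation.** The fixed-physiotherapist columns use 40,000 trials per drift, with variance estimated. The random-intercept columns use 100,000 trials, tau = 1 and known variances.

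| Drift per step | 3-df test misses drift (fixed) | Error, 3-df (fixed) | Error, 3-df (random) | Error, 1-df (random) |
|---|---|---|---|---|
| 0 | – | 0.06 | 0.06 | 0.07 |
| 0.05 | 94% | 0.09 | 0.09 | 0.10 |
| 0.1 | 92% | 0.16 | 0.16 | 0.16 |
| 0.2 | 82% | 0.41 | 0.41 | 0.37 |
| 0.25 | 74% | 0.51 | 0.50 | 0.41 |
| 0.3 | 64% | 0.54 | 0.52 | 0.39 |
| 0.4 | 40% | 0.41 | 0.39 | 0.24 |
| 0.5 | 19% | 0.22 | 0.20 | 0.10 |
| 0.75 | 1% | 0.05 | 0.05 | 0.05 |

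With period always included, error was 0.05 at every drift. Random-intercept runs with tau = 0.44 and tau = 2 peaked at 0.49 and 0.54 (3-df test). A single jump of 0.4 points between periods 2 and 3, instead of a linear drift, gave 0.28.

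**The case against.** The strongest reply is that the protocol already commits to modelling time. The power model has period effects, the challenges section says time effects will be included and warns of the bias, and investigating time is one of the stated reasons for choosing the design. The conditional sentence only says that a within-cluster analysis can be used. The ANOVA sentence may be loose description, and an analysis plan could settle the exact model.

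Much of this stands. A reader might infer that the plan simply discards calendar time. The documents do not support that: they say both things. A reader might also infer that a significance pre-test is specified. It is not; the test and its level are assumptions made here. Nor do the documents support an unconditional claim of several-fold inflation. They give no drift, and the error is a hump: small with little or no drift, and back to 5% once drift is large enough to be detected almost every time.

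What the reply does not remove is the permission itself. It appears twice, once in the section that defines the analysis, and it turns on what is found in the trial's own data. This is not a point left open for an analysis plan, because the protocol states a rule. A plan that follows Statistical methods inherits the rule, and one that does not contradicts it.

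**Conclusion.** The point holds as an internal contradiction combined with a data-dependent permission to drop time. The bias multiplier of 2.0 per unit of drift follows from the design alone. The error rates depend on assumed drift and an assumed test. Inflation is several-fold for drifts of roughly 0.1 to 0.5 points per year with the 3-df test. With the 1-df trend test the peak is lower, about 0.4, and the inflation has fallen to about twofold by 0.5. At no drift or 0.05 it is less than twofold, and at 0.75 it is gone.

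It would also go too far to infer that including period guarantees 5%. That result relies on the protocol's own model of 12 independent physiotherapists, whereas only 3 site pairs are randomised. With an assumed site-pair-by-period SD of 0.2, 0.3 or 0.5 points and no drift, error in the period-adjusted model with fixed physiotherapist effects is 0.09, 0.14 or 0.27. Including period removes the trend bias but does not deal with correlation within site pairs.

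The contradiction should be corrected before analysis, because it affects the primary comparison.

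**What to change.** 1. Delete the conditional sentence in Statistical methods and its repeat in the section on design challenges.
2. Replace the two-group ANOVA description with the model used for the power calculation, and add: *Period (steps 1 to 4) is a fixed categorical factor in every analysis that estimates the intervention effect on patient outcomes and is not removed on the basis of a test.* The limit to intervention-effect analyses matters because the risk-adjustment screening uses step 1 data only, where there is a single period.
3. If a no-period within-cluster estimate is wanted, show it only as a labelled descriptive analysis.

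The cost is a few sentences. The period-adjusted standard error is larger (0.355 against about 0.21), but the sample size was already built on it, so the stated power of 0.805 with 432 observations is unchanged.
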